##### Control Group

The control group receives advice and recommendations for independent physical activity practice at home in order to reach 30 min of moderate intensity physical activity, 5 days a week, as recommended by the World Health Organization (WHO) (current clinical practice).

#### Therapeutic Education Program

Therapeutic patient education programs aim to acquire self-care skills and mobilize or acquire psychosocial skills. In this protocol, we propose four sessions of 2 h, in groups of three to eight patients. The two groups benefit from (1) one session about physiopathology and symptoms of FM by the internal medicine service, (2) one session on physical inactivity and sedentary lifestyle by the myology unit team, (3) one session on the resumption of professional activity by the occupational health service, and (4) one session about the psychological impact and daily routine by the pain center (Figure 3D). All sessions are driven by the coordinating nurse who makes the link between patients and the other health professionals. An individual therapeutic education session will be proposed at V1 and V3 *via* motivational interviewing led by one of the investigator doctors and the nurse/APA teacher duo in order to optimize the durability of the practice of regular physical activity.

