**Figure 3 F3:**
[figure not shown]
FIMOUV program intervention. **(A)** Modalities of aerobic training during the first month of intervention. Each session starts with 10 min warmup and ends with 10 min cooldown. *A continuous training at VT1 can be proposed if the subject's physical capacity does not allow the increase in workloads, as they are made on interval training. (a;b) corresponds to each session of the week; VT1: ventilatory threshold 1; VT2: ventilatory threshold 2. **(B)** Modalities of strength training during the first month of intervention. *Load maximum 50% of 1-repetition maximum if pain evaluation <4/10 at the start of the session. RPE: rating of perceived exertion, Borg modified scale. **(C)** Modalities of relaxation and flexibility training during the first month of intervention. *Hospital Anxiety and Depression Scale >8 for anxiety item. ^$^Fatigue evaluation >7/10 at the start of the session. RHR: resting heart rate. (D) Modalities of therapeutic education program during the first month of intervention.

From the second to third months, each patient is addressed to a relay structure affiliated to the “Sport-Health Houses” of their department to continue a training program for one to two sessions of 60–90 min weekly. Certified by the Ministry of Sports, these health-sport platforms aim to facilitate the maintenance of physical activities among people experiencing health difficulties, with an individualized follow-up. Additionally, a training follow-up booklet will be delivered to ensure the continuity and attendance of training sessions (supervised and autonomous) and evaluate their efficacy on pain and fatigue symptoms thanks to the VAS.

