### Sample Size

Population size is calculated on an expected difference of 20% of the level of MVPA (≥3 METs for metabolic equivalent tasks). Estimating that at baseline, patients are at 3.9 MET-h/week with a standard deviation between 2 and 4 (40), for an alpha risk of 5% and a potency set at 90%, we need to include 150 patients per group; adding an expected dropout rate of 10%, it is necessary to include 165 patients per group to meet the main goal, which means a total of 330 patients.

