### Statistical Analysis

The included population will first be described globally and in groups (test or control), the comparability of the groups will be verified. For quantitative variables, Student's *T*-tests or rank tests (in case of non-normal distribution) will be implemented. The normality of the variables will be checked beforehand with a Shapiro-Wilk test. For qualitative variables, chi-square or Fisher-exact tests (if theoretical numbers are insufficient) will be used. The results will be considered significant at the 5% threshold. The analysis will be carried out in intent-to-treat. An analysis of the main endpoint will be done per protocol. Patients who do not perform 85% of the exercises will be excluded from per-protocol statistical analysis. In addition, we will lead a qualitative study through semistructured individual interviews conducted by a sport and health sociologist. Thirty patients will be recruited in each of the two groups (41, 42). A full transcript will be followed by a thematic and comparative analysis of the cross-data content.

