## Discussion

This study aims to evaluate the efficacy of an optimized care organization within the Loire Territory Hospital Group, illustrated by the sustainability of therapeutic adherence of FM patients. This interventional research will allow us to assess the evolution of behaviors in physical activity after a FM syndrome management based solely on patient education or based on a supervised and adapted practice of physical activity associated with this same therapeutic education program.

Supervised exercise allows a better participation and adhesion to physical activity in sedentary women (43) and an improvement in psychological well-being determined by the result of HADS in FM (44). Improvements up to two times greater than those of unsupervised training can be observed, however without necessarily being maintained for the long-term at 1 year (45). A recent study has explored the experience of the transition from a supervised exercise in the hospital to a community-based unsupervised program in prostate cancer patients, emphasizing the importance of a structured, accompanied and over time monitored relay (46). Dnes et al. (47) identified the barriers and facilitators to participating in community-based exercise opportunities from the perspective of adults with chronic pain, including FM. The main factors identified were participation in groups with similar levels of capabilities, delivered by an instructor able to tailor exercises to chronic pain and recommended by their healthcare provider. Also, in this project, the implementation of physical activity in community programs, chosen by the patient himself/herself according to his/her preferences and availability, could strengthen the integration of physical activity into daily life through the connection with the sports health centers, which have the role of labeling the health-sports club, with groups specific to chronic pathologies delivered by trained instructors.

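### Patients share education groups and, in the test arm only, relay structures, but the named tests and the sample size make no allowance for correlation among patients treated together

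*Protocol article*

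**What the plan says.** Under Randomization and Data Collection, the protocol article randomises patients individually after a multidisciplinary meeting.

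Under Therapeutic Education Program, both arms receive education in shared sessions: "we propose four sessions of 2 h, in groups of three to eight patients". Table 2 places these sessions in the first month. The article does not say whether a group contains one arm or both, or whether the same patients stay together for all four sessions.

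For months 2 and 3, the Test Group section (text after the Figure 3 legend) says "each patient is addressed to a relay structure affiliated to the" Sport-Health Houses, with one to two sessions a week and individualised follow-up. The Discussion describes the clubs involved as having programmes "with groups specific to chronic pathologies delivered by trained instructors". Controls exercise on their own at home. The number of relay structures, and of trial patients in each, is not given.

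Under Statistical Analysis, quantitative variables are compared by Student's t-test, or "rank tests (in case of non-normal distribution) will be implemented"; qualitative variables by chi-square or Fisher tests. No term for education group or relay structure appears. Under Sample Size, "Population size is calculated on an expected difference of 20% of the level of MVPA", "patients are at 3.9 MET-h/week with a standard deviation between 2 and 4" and "we need to include 150 patients per group"; there is no ICC and no design effect.

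**The concern.** Patients who sit in the same education group, or train with the same instructor and peers, may end up with more similar activity levels than patients who do not. One education session is about inactivity and sedentary behaviour, which is close to what the primary endpoint measures. The design is therefore individually randomised with group-delivered treatment, and one layer of the grouping exists in the test arm only. Two-sample tests and a sample size for independent patients do not reflect this.

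The direction of any error depends on a fact the article leaves open:

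- **Arm-specific education groups:** the group effects do not cancel in the arm difference. The unadjusted standard error is too small and the test rejects too often under the null.
- **Groups that mix the arms:** the group effect largely cancels in the arm difference but stays in the residual variance. The unadjusted standard error is too large and precision is lost.
- **Relay structures:** these cluster the test arm alone, however education groups are formed, so the two arms can have different error structures.

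What is at stake is the validity of the primary test's 5% level and the meaning of the stated 90% power.

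**Working it through.** **Inputs from the protocol article.** Difference 20% of 3.9 = 0.78 MET-h/week; SD given only as 2 to 4; alpha 5% (taken as two-sided, since sidedness is not stated); power 90%; 150 per group before dropout; education groups of 3 to 8.

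**Assumptions.** ICC 0.01 to 0.10; mean group size m = (3 + 8)/2 = 5.5; a continuous endpoint.

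**Step 1: the plan's own figure.** n per group = 2 × (SD × (1.960 + 1.282)/0.78)². This gives 139 at SD 2, 311 at SD 3 and 553 at SD 4. The figure of 150 is not reproduced at any of these. It needs SD = 0.78/(3.242 × √(2/150)) = 2.08, which lies inside the stated range but is not itself stated. All power figures below use this value, so that they start from exactly 90%.

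**Step 2: arm-specific education groups.** The formulas are:

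- Design effect: DE = 1 + (m − 1) × ICC
- True type I error of the unadjusted test: 2 × P(Z > 1.96/√DE)
- Power of a correctly adjusted test at 150 per group: Φ(3.242/√DE − 1.96)

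| ICC | DE (m = 5.5) | Effective n per group | Type I error, unadjusted test | Power, adjusted test |
|---|---|---|---|---|
| 0.01 | 1.045 | 144 | 5.5% | 89% |
| 0.02 | 1.09 | 138 | 6.0% | 87% |
| 0.05 | 1.225 | 122 | 7.7% | 83% |
| 0.10 | 1.45 | 103 | 10.4% | 77% |

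At the extreme of m = 8 and ICC 0.10, DE = 1.70, type I error is 13% and adjusted power is 70%. At m = 3 and ICC 0.01, DE = 1.02 and the figures are 5.2% and 89%.

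**Step 3: which test each figure belongs to.** The last two columns describe different tests. If the planned unadjusted test is used, its probability of rejecting under the assumed effect is Φ((3.242 − 1.96)/√DE). That is Φ(1.282/1.204) = 86% at DE 1.45 and Φ(1.282/1.304) = 84% at DE 1.70. The planned test therefore pays mainly in type I error. The fall to 77% or 70% is the price once the error rate is restored.

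**Step 4: groups that mix the arms.** With each group split evenly between arms, the true variance of the difference is (1 − ICC) times what the unadjusted test assumes. The true type I error is 2 × P(Z > 1.96/√(1 − ICC)): 4.9% at ICC 0.01 and 3.9% at ICC 0.10. The test is then conservative.

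**Step 5: clustering in the test arm only.** The variance of the difference is multiplied by (DE + 1)/2. Relay sizes are unknown, so the design effects of Step 2 serve only as placeholders. For DE 1.045 to 1.45 the multiplier is 1.02 to 1.225, type I error 5.3% to 7.7% and adjusted power 89% to 83%. For DE 1.70 it is 1.35, 9.2% and 80%.

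**The case against.** The strongest reply is that nothing here has been shown to go wrong. A reader might infer that the planned standard error and the stated power are wrong as they stand. The documents do not support that: any error needs a non-zero ICC, and none is given. The outcome is each patient's own accelerometry at 1 year, months after the shared sessions end, and individual motivational interviews take place at V1 and V3. These features argue for a low ICC, and nothing in the article supports 0.10 in particular. This part of the reply stands.

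A reader might also infer that education groups inflate the type I error. That holds only if they are arm-specific, which the article does not say; mixed groups push the other way. A third tempting reading is that the planned test suffers both the 10% type I error and the 77% power. It does not, as Step 3 shows.

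The relay argument has limits too. Follow-up is described as individualised, patients choose their programme, and trial patients may be spread so thinly that few share a structure. But individual follow-up does not remove a shared instructor or peer group, and the Discussion does describe groups.

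Finally, the full protocol or the SAP may specify a cluster adjustment. That would settle the analysis. It would not change a sample size already fixed without allowance for clustering, and it would work only if group and structure are recorded while the trial runs.

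**Conclusion.** The point holds in a limited form: the tests and sample size that the article fixes make no allowance for correlation among patients treated together, although the design puts patients in shared groups in both arms and in shared structures in one arm. Whether this distorts the primary test, by how much and in which direction cannot be settled from the article.

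The illustrative range runs from negligible (about 1 point of power and half a point of type I error at ICC 0.01) to material (type I error about 10%, adjusted power 77%, at ICC 0.10 with arm-specific groups of 5.5). It rests on the assumed ICC, the assumed grouping and the back-solved SD of 2.08.

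The stated SD range is a separate and larger threat to power: 150 per group gives 92% at SD 2, 61% at SD 3 and 39% at SD 4. It leaves little margin to absorb a clustering loss. The clustering point is worth acting on because the remedy is cheap and the relay clustering remains possible even if education groups mix the arms.

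**What to change.** 1. State whether education groups are arm-specific or mixed, and whether membership is constant over the four sessions.
2. Record each patient's education group and, in the test arm, relay structure. If membership changes, record the group at each session and define in advance which one enters the model.
3. Analyse the primary endpoint with a partially nested mixed model: a random intercept for education group, and a relay-structure effect in the test arm only. Cluster-robust standard errors with a small-sample correction are an alternative. If the 7.5 MET-h/week threshold under Assessment Measures is the endpoint, use the binary equivalent.
4. Keep the unadjusted test as a sensitivity analysis.
5. Report power over an assumed ICC range, with the SD used stated.

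The cost is two identifier fields in the electronic record and a paragraph of analysis wording. The downside is slightly wider intervals, a small loss of degrees of freedom and a slightly less favourable stated power.

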### Assessment Measures

The primary outcome of interest will be the long-term therapeutic adherence of FM patients evaluated from an objective measure of physical activity (mean measured from 7 days of accelerometry; Actigraph GT3x, Pensacola, Florida, USA) 1 year after the setup of the organization of care offering initiation and support of APA during 3 months. This sustainability will result in a level of physical activity ≥7.5 MET-h/week at 1 year, corresponding to 150 min of moderate intensity physical activity per week, which is consistent with WHO recommendations.

The secondary objectives will evaluate the impact on the lifestyle (average time of physical activity and sedentary behavior, measured by accelerometry during 7 days), health status, fatigue, sleep, psychic distress, muscular strength and endurance, physical capacity, tolerance to pain and fatigue during training sessions, membership to physical activity, evaluation of the differential cost-effectiveness ratio, and finally an estimate of the budgetary impact of this care strategy.

Details and timetable are shown in Table 2.

**Table 2 T2:** Assessment measures timetable.

	**Inclusion visit V1**	**Intervention 1st month**	**Post-intervention visit V2**	**Intervention 2nd and 3rd months**	**Post-intervention visit V3**	**Intermediate visit V4**	**Final visit V5**

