## Abstract

**Introduction:** Fibromyalgia (FM) is characterized by multiple symptoms including pain, fatigue, and sleep disorders, altering patient's quality of life. In the absence of effective pharmacological therapy, the last European guidelines recommend a multidisciplinary management based on exercise and education. Thus, our main objective was to measure the effectiveness of a healthcare organization offering a specific program of adapted physical activity combined with a therapeutic education program for FM patients.

**Methods and Analysis:** The From Intent To Move (FIMOUV) study will recruit 330 FM patients randomized into two groups: test and control. The test group will benefit from a 1-month mixed exercise training program supervised at the hospital, followed by 2 months in a community-based relay in a health-sport structure. In addition, each of the two groups will benefit from therapeutic patient education sessions. The main endpoint is the measurement of the level of physical activity by accelerometry at 1 year. The secondary endpoints concern adherence to the practice of physical activity, impact on lifestyle, state of health, and physical capacity, as well as an estimate of the budgetary impact of this management strategy.

**Discussion:** This interventional research will allow us to assess the evolution of behaviors in physical activity after an FM syndrome management based solely on patient education or based on a supervised and adapted practice of physical activity associated with this same therapeutic education program. It seems to be the first study evaluating the impact of its intervention on objective data for measuring physical activity and sedentary behavior *via* accelerometry among FM patients.

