Despite the absence of accurate recommendations on training modalities, as defined by the ACSM, a personalized and mixed training seems to be the best practice according to the EULAR recommendations (8), and it is also this type of training that is recommended for people suffering from chronic pain (35). In France, there are no professional recommendations of good practice for the management of FM. The health insurance recommends to physicians to give advice for the progressive upturn of physical activity for each person with FM, “according to its means.”

However, European and French recommendations agree to promote patient education to increase “understanding of the complex nature of the interactions between neurobiological processes, behaviors, and symptoms (36).” It showed beneficial impact on pain and pain catastrophizing (37) despite the different educational strategies. Moreover, an education program would be all the more effective if it is combined with an adapted physical activity (APA) program (38, 39).

Then, the problem is to know if simple advice for physical activity is sufficient (as recommended by the French health insurance and commonly performed in consultation) or if an adapted and supervised physical activity (as recommend by the EULAR) would not be more beneficial as a first intention. Thus, in this study, we want to optimize the care pathways of patients suffering from FM by offering a supervised APA program added to therapeutic patient education sessions. This is a prospective, multicenter, controlled, randomized, open-label intervention in two groups. The primary objective of this study is to measure the effectiveness of a healthcare organization offering APA for FM patients through an objective measure of physical activity at 1 year (average measured from 7 days of accelerometry). The protocol has been written according to the Standard Protocol Items: Recommendations for Interventional Trials guidelines.

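### The primary outcome is described both through a 7.5 MET-h/week level and as an activity level without a threshold; only a difference in level was sized, and its planned effect falls well short of 7.5

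*Protocol article*

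**What the plan says.** All references are to the Protocol article.

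- **Assessment Measures** names long-term adherence as the primary outcome, evaluated from a 7-day accelerometer average one year after the care pathway is set up. It continues: "This sustainability will result in a level of physical activity ≥7.5 MET-h/week at 1 year", and equates that level with 150 minutes of moderate activity a week and with WHO advice. The next paragraph lists among the secondary objectives "impact on the lifestyle (average time of physical activity and sedentary behavior, measured by accelerometry during 7 days".
- **Abstract**: "The main endpoint is the measurement of the level of physical activity by accelerometry at 1 year". No threshold is given.
- **Introduction**, primary objective: effectiveness is measured "through an objective measure of physical activity at 1 year (average measured from 7 days of accelerometry". Again there is no threshold.
- **Sample Size**: "Population size is calculated on an expected difference of 20% of the level of MVPA". At baseline "patients are at 3.9 MET-h/week with a standard deviation between 2 and 4". The error rates are "for an alpha risk of 5% and a potency set at 90" per cent. The result is 150 per group, raised to 165 for 10% dropout. No responder rate appears.
- **Statistical Analysis** gives t or rank tests for quantitative variables. It then says "For qualitative variables, chi-square or Fisher-exact tests" (the latter for small expected counts). Neither kind of test is assigned to the main endpoint.

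**The concern.** Assessment Measures gives the primary outcome a cut-off, and its list of secondary objectives already contains average activity time. A reader of that section could reasonably take the primary result to be whether patients reach 7.5 MET-h/week. A reader of Sample Size would take it to be a difference in activity level.

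The choice changes what the trial can show. If the cut-off is primary, the stated 90% power belongs to a different endpoint. If the level is primary, a significant result of the planned size is 0.78 MET-h/week. At 3 METs that is 0.78 / 3 = 0.26 h, or about 16 minutes a week, and it would not by itself show that patients sustain the WHO level. The trial is open-label, so it matters that the primary variable is fixed unambiguously before results are seen.

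**Working it through.** **Inputs from Sample Size:** baseline mean 3.9 MET-h/week; SD between 2 and 4; difference 20%; alpha 5%; power 90%; 150 per group. **From Assessment Measures:** threshold 7.5 MET-h/week (2.5 h × 3 METs = 7.5).

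**Assumptions, not in the article:** two-sided test; the 20% is relative; the 1-year control mean equals the baseline mean; the distribution shape and SD behaviour are as listed in step 4.

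**1. Planned effect against the threshold.** The difference is 0.20 × 3.9 = 0.78, so the test-group mean is 3.9 + 0.78 = 4.68, and 4.68 / 7.5 = 62%. This step needs no distribution.

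**2. Reproducing 150 per group as a comparison of means.** n = 2(1.960 + 1.282)² SD² / 0.78² ≈ 34.5 × SD².

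- SD 2 gives 139, SD 3 gives 311 and SD 4 gives 553.
- Solving for n = 150 gives SD ≈ 2.08.
- Reading the 20% as percentage points between two proportions, with control rates of 10-50%, gives 82-130 per group, or 92-140 with continuity correction. It never gives 150.

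So 150 is recovered from a comparison of means, at one SD near the bottom of the stated range, and not from the responder calculations tried.

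**3. Power for the mean at 150 per group.** Power = Φ(0.78 / (SD√(2/150)) − 1.960).

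- SD 2: Φ(3.378 − 1.960) = 92%
- SD 3: Φ(2.252 − 1.960) = 61%
- SD 4: Φ(1.689 − 1.960) = 39%

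**4. Power for the proportion at or above 7.5, at 150 per group.** The responder rate in each arm is P(X ≥ 7.5). With a normal shape and SD 2, the control rate is 1 − Φ((7.5 − 3.9)/2) = 1 − Φ(1.80) = 3.6%, and the test rate is 1 − Φ((7.5 − 4.68)/2) = 1 − Φ(1.41) = 7.9%. Power is from the two-sided pooled two-proportion test. Each cell shows control v test rate, then power.

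| Shape, SD behaviour | SD 2 | SD 3 | SD 4 |
|---|---|---|---|
| Normal, equal SDs | 3.6% v 7.9%: 36% | 11.5% v 17.4%: 30% | 18.4% v 24.0%: 22% |
| Gamma, equal SDs | 5.6% v 9.1%: 22% | 11.5% v 15.8%: 18% | 14.9% v 19.1%: 16% |
| Lognormal, equal SDs | 5.5% v 8.8%: 19% | 9.7% v 13.6%: 19% | 11.6% v 15.7%: 18% |
| Normal, test SD 20% larger | 3.6% v 12.0%: 78% | 11.5% v 21.7%: 66% | 18.4% v 27.8%: 49% |
| Gamma, test SD 20% larger | 5.6% v 12.3%: 53% | 11.5% v 18.0%: 35% | 14.9% v 20.3%: 23% |
| Lognormal, test SD 20% larger | 5.5% v 11.2%: 42% | 9.7% v 15.1%: 29% | 11.6% v 16.4%: 22% |

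The range is therefore 16-36% with equal SDs and 22-78% when the SD grows with the mean. At SD 2, 3 and 4, reaching 90% would need 606 to 1,665 per group in the first case and 212 to 1,118 in the second.

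**The case against.** The strongest reply is that the article never defines a binary endpoint. The threshold sentence can be read as the result the authors hope for, and the measurement itself is a 7-day average. The chi-square test is offered for qualitative variables in general. Naming the primary test is commonly left to the full protocol or SAP, which are not shown. This stands. A reader might infer that the primary outcome is explicitly a responder rate tested by chi-square, or that two primary tests at 5% are planned; the text supports neither. What it contains is an unresolved ambiguity. Even on the softer reading, a hoped-for level of at least 7.5 conflicts with a planning mean of about 4.68.

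The contrast between the sections must not be overdrawn either. The Abstract's wording fits both readings. The averages in the Introduction and Assessment Measures are each patient's 7-day average, not group means. Only Sample Size clearly points to a continuous comparison.

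A reader might also take 16-36% as the trial's power for the threshold. The article does not fix that figure. Controls receive education and activity advice, so their 1-year mean may differ from 3.9. A normal shape with mean 3.9 and SD 4 also puts about 16% of patients below zero. If the spread grows with the mean, power is higher. What survives is that no scenario tested reaches 90%.

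Finally, it would be too generous to say that the sample size fits the mean. It does so only near SD 2.0-2.1.

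**Conclusion.** The point holds as an ambiguity in the primary endpoint, together with a mismatch between the threshold and the planning assumptions. The description attached to the primary outcome refers to 7.5 MET-h/week. The sizing refers to a difference that, taking baseline as the control mean, leaves the test group at about 62% of that level.

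If the threshold is primary, the stated 90% power is not delivered in any scenario tested. The specific values (16-36% with equal SDs; 22-78% with the SD growing 20% with the mean) depend on the assumed shape, SD behaviour and control mean. If the mean is primary, 90% holds only for an SD up to about 2.08, and over most of the stated SD range 150 per group is too few.

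The point deserves correction before analysis because it concerns which variable is primary. The conflict between 4.68 and 7.5 is firm under the baseline-as-control reading; the threshold power figures are indicative.

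**What to change.** 1. Name one primary variable and its test. The natural choice is accelerometer MVPA in MET-h/week at V5, compared between groups as a continuous variable, because the sample size is built on it. Reword the threshold sentence in Assessment Measures to match, and say how this variable differs from the average activity time listed as secondary.
2. Make the proportion at or above 7.5 MET-h/week a named secondary endpoint, reported as a difference with a confidence interval and stated as not powered. State that a significant mean difference alone will not be reported as sustained adherence at the WHO level.
3. State and justify the single SD behind 150 per group (about 2.08), and restate power for the mean over the given range: about 92% at SD 2, 61% at SD 3 and 39% at SD 4.
4. If the sponsor prefers to keep the threshold as primary, state the responder rates assumed in each group and the power that 150 per group gives for them.

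Items 1 to 3 cost a wording amendment and no new data. They do not by themselves secure 90% power: if the justified SD is well above 2.08, the lower power must be declared or the sample size revisited.
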